### Interim analysis

An interim analysis will be performed by the Trial Management Committee after 576 participants have undergone their first embryo transfer and completed three months of follow-up. The results will be reported to the principal investigator for decision-making. The principal investigator will have the right to terminate participant enrollment in the following situations: (1) strong evidence from this study or any other studies demonstrates that the intervention (niEVT) leads to less benefits gained and more AEs; and (2) strong evidence shows that the intervention is superior to the control, or vice versa.

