## Methods

### Trial design

This protocol is for a multicenter, double-blinded, randomized, controlled trial that will be conducted in China (Fig. 1). This protocol was revised several times by experts to form this final version before trial commencement. Patient recruiting is being carried out simultaneously in eight reproductive medical centers, including the First Medical Center of PLA General Hospital (PLAGH), the Sixth Medical Center of PLA General Hospital (6MC-PLAGH), the Air Force Medical University-Tangdu Hospital (Tangdu Hospital), the 900th Hospital of the Joint Logistics Team (900 Hospital), the Third Affiliated Hospital of Sun Yat-Sen University (3AH-SYSU), Henan Provence People’s Hospital (Henan-PPH), the University of Hong Kong-Shenzhen Hospital (HongKong-SH), and the Zhuhai Center for Maternal and Child Health Care (Zhuhai-CMCHC). Three rounds of clinical inspections will be conducted in every reproductive medical center by a trial management committee (TMC). The aim of the clinical inspections will be to ensure that the study is performed according to the protocol and that the data are collected and recorded in a timely manner.

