### Randomization and masking

Randomization and allocation will be controlled centrally by a web-based niEVT administration database. The randomization will be stratified by fertilization protocol (IVF, ICSI) and by age (< 35, ≥ 35 years). Eligible patients will be independently allocated to either the intervention group (niEVT) or control group (morphological assessment) in a 1:1 ratio using a dynamical stratified blocked randomization algorithm with a block of 6. Regarding patient allocations, the embryologist, research assistants, clinicians, and patients will be blinded.

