### Data collection and management

The clinical data of 1152 patients will be collected, with 576 patients in each group. Data will be collected and stored in two forms, including paper files and electronic files. All clinical data will be first collected and recorded in paper files, including the signed consent form and all types of medical records. Then, the medical records and the niEVT results will be transformed into electronic files and stored in the central niEVT administration database (an online website developed for data management). For privacy protection, patient identification codes will be assigned to every participant and used to link to the clinical data. All paper files will be stored in the reproductive medical centers for five years, and only the local investigators, clinicians, and research assistants will have access to these files. Only the principal investigator and statistician of this trial will have full access to all the data (except for patient privacy information) of the eight reproductive medical centers.

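### Interim results go to a principal investigator with full data access and the right to stop enrolment, so those leading the trial can know the comparison while it is still running

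*Protocol article*

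**What the plan says.** All places are in the Methods of the protocol article.

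- **Interim analysis.** "An interim analysis will be performed by the Trial Management Committee after 576 participants have undergone their first embryo transfer" and have completed three months of follow-up. Then: "The results will be reported to the principal investigator for decision-making". The power to stop is given to one role: "The principal investigator will have the right to terminate participant enrollment in the following situations". One situation is that evidence from this or other studies shows less benefit and more adverse events with niEVT. The other is that "strong evidence shows that the intervention is superior to the control, or vice versa".
- **Data collection and management.** "Only the principal investigator and statistician of this trial will have full access to all the data", for all eight centres, with patient privacy information as the only exception. The same section says that "the medical records and the niEVT results will be transformed into electronic files and stored in the central niEVT administration database".
- **Randomization and masking.** Here "the embryologist, research assistants, clinicians, and patients will be blinded". The principal investigator, the statistician and the Trial Management Committee are not on this list.
- **Trial design.** The trial is labelled double-blinded, and "Three rounds of clinical inspections will be conducted in every reproductive medical center by a trial management committee".
- **Adverse events.** Serious adverse events go at once to the principal investigator and the Trial Management Committee.

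**The concern.** A blinded trial normally keeps accumulating results by arm away from those who direct it, so that nothing they do after the look can be a response to the observed difference. Here the text sends the interim results to the person who leads the trial and who decides whether enrolment goes on. It also gives that person full data access with no date attached.

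Two things are at stake. The first is conduct after the look: recruitment effort, contact with centres and readiness to change procedures can all shift once the direction of effect is known. The second is the stopping decision. As described, it turns on whether evidence is strong, and it is made by someone who sees the arms. A finished trial could not show afterwards that either was free of that knowledge.

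**Working it through.** **1. The plan's own figures.** Inputs from the section on sample size: live birth 50% and 60%, two-sided alpha 5%, power 90%, 10% loss. With the pooled-variance formula, n per arm = [1.960·√(2·0.55·0.45) + 1.2816·√(0.50·0.50 + 0.60·0.40)]² / 0.10² = (1.379 + 0.897)² / 0.01 ≈ 518.04. Rounded up this is 519 per arm, or 1038 in total, against 1036 stated (2 × 518). Then 1036 / 0.90 = 1151.1, which gives the stated 1152. The totals used below are therefore sound.

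**2. Do the interim results have to be by arm?** The article does not call the report unblinded. Superiority in either direction can be judged only by comparing arms. Less benefit and more adverse events can also be judged from this study only by comparing arms; evidence from other studies would not need that. So for any decision based on this trial's own data, the results that reach the principal investigator must be comparative.

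**3. Does the access rule close the gap?** No. It excepts only privacy information and names no date. The article does not say in terms that the allocation list is visible, and niEVT results alone need not reveal allocation, since collection of spent medium is described before the arms are separated. But access to all the data, read as written, includes group assignment.

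**4. Do the two sections agree?** Set side by side:

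| Section | Who holds the data |
|---|---|
| Data collection and management | Full access for the principal investigator and statistician only |
| Interim analysis | The Trial Management Committee performs the comparative analysis |

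The committee cannot compare arms without data by arm, and the access rule does not include it. The article does not say whether it works from a report prepared by someone else.

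**5. How many women are concerned?** Outside the interim set: 1152 − 576 = 576, or 50%. (The abstract gives 1140, which would leave 564.) This is a ceiling, because the look comes three months after the 576th first transfer. Assume that first transfers run evenly over the 24 months that the abstract gives for enrolment: 1152 / 24 = 48 a month, so 3 × 48 = 144 more women have been transferred by then, and 576 − 144 = 432 remain. The pace is an assumption. The range is:

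| First transfers per month | Transferred in the three months | Still to have a first transfer |
|---|---|---|
| 24 | 72 | 504 |
| 48 | 144 | 432 |
| 96 | 288 | 288 |

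Fewer still remain to be enrolled, since enrolment precedes the frozen transfer. Some women inside the interim set may also go on to a second or third transfer after the look; the article gives no basis for a count.

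**6. What would the look show?** Live birth requires 28 completed weeks of gestation. Three months after transfer is about 13 weeks, so for the most recently transferred women the comparison rests on pregnancy data, not on the primary outcome.

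**The case against.** The strongest reply is that the article never claims that its leadership is blinded. The masking section lists four roles, and neither the principal investigator nor the committee is among them. **This stands.** A reader might infer that the double-blind label is false or that the masking section is contradicted. The documents do not support that: nothing shows that a listed role learns the allocation, and the article does not say whether the principal investigator or any committee member also treats patients.

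Second, the routes to bias are narrow. Allocation is central, the transfer order follows a fixed ranking with random tie-breaks, the clinical reports show neither niPGT-A results nor grades, and live birth is an objective outcome. **This stands too**, and it limits the effect on the primary comparison. It does not cover later conduct or the decision to stop.

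Third, a reader might infer particular harm to adverse event assessment, because serious events go to the principal investigator and the committee. The section on adverse events gives them receipt only, with no adjudication role, and events are recorded whether or not they are thought related. The inference is not supported.

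Fourth, a reader might take the principal investigator to be the sole decision-maker. The article names no other, but it does not exclude one.

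Fifth, committee membership and the form of the report may be set out in the full protocol, and their absence is no finding. The point rests instead on what the article does state: results go to the principal investigator for decision, and that person's access has no time limit.

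**Conclusion.** The point holds as a weakness of interim governance. The article affirmatively routes the interim results to the principal investigator, gives that person a discretionary right to end enrolment on comparative grounds, and does not defer full data access to database lock. Those leading the trial can therefore know the comparison while it is running. Separately, the sections on data access and interim analysis do not agree on who may hold data by arm.

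At most 576 women lie outside the interim set. About 432 would still await a first transfer on even accrual, or 288 to 504 if the pace were double or half that. The size of any bias cannot be derived from the document. It is likely to be limited for live birth; the exposure lies in conduct after the look and in the stopping decision.

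The conclusion rests on two readings: that stopping on this trial's own evidence requires results by arm, and that access stated without a date applies during the trial. It does not rest on any failure of blinding among patients, embryologists or treating clinicians. The change is worth making because it is cheap now and the gap cannot be repaired once the look has taken place.

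**What to change.** 1. **Data collection and management:** state that until database lock only the trial statistician has access to group assignment and to data by arm. The principal investigator keeps access to data that do not reveal the arm.
2. **Interim analysis:** state that the statistician prepares a closed report for the Trial Management Committee, and that the principal investigator receives only a recommendation to continue or to stop enrolment, without figures by arm.
3. These two changes also reconcile the sections, because the committee then works from the statistician's report and needs no database access of its own.

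The cost is one access setting in the database and a few sentences, using the existing statistician and committee. No treatment, endpoint or sample size changes. The small downside is that the principal investigator acts on a recommendation without seeing the figures behind it. The committee would still see results by arm and still inspect the centres. Requiring members who do not inspect might need people whom the article does not show to exist, so it is not asked for here.

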## Discussion

PGT-A was demonstrated to reduce the miscarriage rate and improve the live birth rate after the first embryo transfer in IVF patients, especially for patients of advanced maternal age [23, 24]. niPGT-A is expected to be an alternative to PGT-A [12, 13]. Some clinicians as well as commercial niPGT-A suppliers assume that niPGT-A will bring a similar benefit as PGT-A to patients. However, strong clinical evidence to support or reject this assumption is lacking. The current trial is a well-designed RCT with a large sample size that is expected to fill the knowledge gap.

The study population will be stratified by fertilization method and by age. Based on our preliminary data, embryo washing carefully on Day 4 plus a modified PicoPLEX whole genome amplification protocol (Xu et al., 2022) will help to greatly reduce the genetic testing bias results from maternal/paternal DNA contamination [25]. We speculate that the fertilization method will have limited effects on the final clinical outcomes. However, an inaccurate or even a false niPGT-A result is possible because it is impossible to eliminate the bias completely under the current circumstances. In addition, we are confident that patients of advanced maternal age are very likely to benefit from noninvasive embryo viability testing (niEVT). A higher prevalence of chromosome abnormalities is likely to occur in these patients [26–29]. In addition, a previous study showed that the clinical outcomes of conventional IVF were inferior to those of PGT-A in patients of young maternal age [30]. Based on these results, we speculate that patients of young maternal age will not significantly benefit from the intervention.

Economic evaluation will not be performed in this study. Taking the sampling process into consideration, niPGT-A has an obvious advantage over PGT-A, which relies on special equipment and professional embryologists to perform embryo biopsy [11, 13]. Apart from cost-effectiveness, the most important significance of niPGT-A is that it completely prevents the short-term and long-term risks resulting from embryo biopsy.

To conclude, this large RCT will compare the clinical outcomes between niPGT-A and conventional IVF. This study will answer the question of whether and which patients will benefit from niEVT based on strong clinical evidence.

## Data Availability

The full trial protocol is available upon request to the corresponding author. The trial team is responsible for the final trial dataset. This dataset and the statistical code can be made available upon reasonable request after consideration by the trial management group.

## Abbreviations

AEs: A training for adverse events
BF: Blastocoel fluid
cfDNA: Cell-free DNA
ChiCTR: Chinese Clinical Trial Registry
CMH: Cochran-Mantel-Haenszel
ET: Embryo transfer
ICSI: Intracytoplasmic sperm injection
ITT: Intention-to-treat
IVF: In vitro fertilization
niEVT: Non-invasive embryo viability testing
niPGT-A: Non-invasive PGT-A
PGT-A: Preimplantation genetic testing for aneuploid
RCT: Randomized controlled trial
SAE: Serious adverse events
SBCM: Spent blastocyst culture medium
SD: Standard deviations
TE-biopsy: Trophectoderm biopsy
TMC: Trial Management Committee
